## **Background and Significance**

The objective is to provide support to assist impaired ventilation in apnea of prematurity (AOP). Recurrent apnea and accompanying resultant intermittent hypoxic (IH) episodes are significant concerns commonly encountered in premature infants, and optimal management is a challenge to neonatologists. AOP is defined as “a pause of breathing for more than 15-20 seconds or accompanied by oxygen desaturation ( $SpO_2 < 80\%$  for  $> 4s$ ) and bradycardia (heart rate  $< 2/3$  of baseline for  $> 4s$ ), in infants born less than 37 weeks of gestation [Morielle G et al., 2010]. When these pauses are longer ( $> 15s$ ), they are frequently prolonged by obstructed inspiratory efforts, most likely secondary to loss of upper airway tonic activity [Martin RJ et al., 2012]. In extremely low birth weight (ELBW) infants, the incidence of IH progressively increases over the first 4 weeks of postnatal life, followed by a plateau and subsequent decline between 6-8 weeks.

The incidence of AOP correlates inversely with gestational age and birth weight. Nearly all infants born  $< 29$  weeks gestation or  $< 1,000$  g [Robertson CM et al., 2009], 54% at 30 to 31 weeks, 15% at 32 to 33 weeks, and 7% at 34 to 35 weeks gestation exhibit AOP [Martin RJ et al.]. Both animal and human evidence show that immature or impaired respiratory control and the resultant IH exposure contribute to a variety of pathophysiologic issues via pro-inflammatory and/or pro-oxidant cascade as well as cellular mechanisms, e.g., apoptosis, leading to acute and chronic morbidities (e.g. retinopathy of prematurity, altered growth and cardiovascular regulation, disrupting zinc homeostasis which hampers insulin production and there by predisposing to diabetes in later life, cerebellar injuries and neurodevelopmental disabilities) [Martin RJ et al., 2004, Pae EK et al., 2011, 2014].

Current standard of care for AOP includes prone positioning, continuous positive airway pressure (CPAP) or nasal intermittent positive pressure ventilation (NIPPV) to prevent pharyngeal collapse and alveolar atelectasis, and methylxanthine therapy (caffeine, theophylline), which is the mainstay of treatment of central apnea [Reher et al., 2008; Pantalitschka T et al., 2009; Moretti C et al., 2012; Henderson-Smart DJ et al., 2010]. Apart from prone positioning, none of these interventions are optimal for early development. CPAP masks will distort the bony facial structure in early development, and methylxanthine interventions pose serious questions of neural development interactions.

## **Hypothesis**

Applying slight vibration to the limbs will reduce the number of breathing pauses in apnea of prematurity, thus improving the supply of oxygen to the body.

## **Study Design**

### **Subjects**

Number of Infants:  $\leq 25$

Inclusion Criteria:

1. Gestational age  $> 23$  weeks,  $< 34$  weeks
2. At least 1 week old at recruitment

3. Diagnosis of apnea of prematurity (AOP)
4. Caffeine treatment will not be an exclusion
5. Race, sex, or national origin will not be reasons for exclusion.

**Exclusion Criteria:**

1. Infants with major congenital anomalies/malformations which will influence central nervous system and long-term outcomes in these infants, such as cardiac anomalies (except for PDA or VSD) or major neurological malformations, like meningoencephalocele, holoprosencephaly etc.
2. Neonates who have apnea from airway issues like laryngomalacia, tracheomalacia or severe GERD
3. Neonates with history of hypoxic ischemic encephalopathy or Grade IV IVH will be excluded

After parent/guardian consent has been obtained by the study team, the infant will be randomized by coin flip to start with or without vibration. Subjects will be monitored for 24 hours with the existing standard NICU monitors (GE HealthCare Systems). Small vibration devices will be placed on one hand and one foot. Those vibration devices will deliver continuous mild vibration in a 6 hour ON/OFF or OFF/ON sequence, for a total of 24 hours. In all subjects, we will continuously collect heart rate via 3 leads, thoracic wall movement for detection of respiratory patterns, and oxygen saturation using pulse oximetry, from the existing NICU GE HealthCare monitors. Breathing pauses [episodes >3-5 sec in duration (short pauses), and > 5sec in duration (long pauses)], IH episodes (the number of events in which O2 saturation fell below 90%, 88%, and 85% for at least 5 sec), and bradycardia episodes [occurrences of heart rate declines to less than <110 bpm (mild bradycardia), and < 100 bpm (moderate bradycardia) for at least 5 sec] will be examined. The total number and duration of breathing pauses, IH episodes and bradycardia episodes will be evaluated using LabView Software (National Instruments, Austin, TX), as well as LabChart Pro (AD Instruments), with proprioceptive stimulation (total of 12 hours) and without stimulation (total 12 hours), in each study subject.

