**Vibration Device**

The research involves investigational use of an unapproved device. This vibratory device consists of small disk that will be attached to the skin, and thus it is non-invasive. The device is operated by a 9-volt battery and there is no exposed conductive material. The output current is fused for protection. The vibrations that this device generates do not cause discomfort or pain. The device causes a slight pressure similar to the standard pulse oximeter probe; however, it should not cause long-lasting discomfort. Other tests have shown that the vibration does not interfere with sleeping patterns. The device has been reviewed and approved by the Clinical Engineering Division at UCLA, Principal Electronics Technician for the Neonatal ICU, [name] and has been deemed safe to use in human subjects.

The vibration device consists of two components: (1) small vibrating disks, which are taped to the skin over

[figure not shown]

proprioceptive fibers in the hand and foot, and (2) stimulation device containing a low voltage battery which powers the vibration motors (Figure 1). The vibration motor is similar to those found in powered toothbrushes or cell phones. The stimulation patterns are established and transmitted to the stimulation unit via Bluetooth from an Android tablet. There is no visible blue tooth connection on the device. Blue tooth signal will only be used at the start of the study to establish the parameters. This will be done remotely and away from the patient/NICU, and the Bluetooth signal will be turned off. Once the device is placed on the patient and/turned on, no Bluetooth connection exists. The android device will not be placed in the NICU by the baby's bedside. The device has been reviewed by the Clinical Engineering Division at UCLA, Principal Electronics Technician for the Neonatal ICU, [name] (under [name], Director).

The vibration devices will be attached one to the surface of the palm of the hand and one to the ankle.

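### The protocol provides no masking of bedside staff or of those processing the recordings to vibration ON or OFF, although its off-unit device set-up would make some masking cheap

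*Protocol*

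**What the plan says.** The conduct of the study is set out in the Study Design text that follows the exclusion criteria. After consent, "the infant will be randomized by coin flip to start with or without vibration". On the equipment it says "Small vibration devices will be placed on one hand and one foot", and then "Those vibration devices will deliver continuous mild vibration in a 6 hour ON/OFF or OFF/ON sequence, for a total of 24 hours". Heart rate, chest wall movement and oxygen saturation come from the standard unit monitors. Breathing pauses, desaturations and bradycardias are defined by numeric thresholds and minimum durations of a few seconds. Their number and duration "will be evaluated using LabView Software (National Instruments, Austin, TX), as well as LabChart Pro (AD Instruments"), and are compared "with proprioceptive stimulation (total of 12 hours) and without stimulation (total 12 hours), in each study subject".

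The Vibration Device section says that the stimulation parameters are set by tablet at the start: "This will be done remotely and away from the patient/NICU, and the Bluetooth signal will be turned off". It adds: "The android device will not be placed in the NICU by the baby's bedside". It describes the stimulus by analogy: "The vibration motor is similar to those found in powered toothbrushes or cell phones".

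The Analyses section plans within-infant paired t-tests between periods with and without stimulation, in at most 25 infants. It describes the study as a pilot to determine effectiveness before a larger randomised trial.

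No section mentions blinding, masking, a sham, withholding the sequence from staff, or hiding condition labels when the recordings are processed.

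**The concern.** In a within-infant comparison, the treatment effect is clean only if vibration is the one thing that differs systematically between ON and OFF. Knowledge of the condition can add a second difference in two places.

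- **At the bedside.** The events last seconds, and duration is itself an outcome. A nurse who knows the condition may be quicker or slower to touch or reposition the infant. That can alter how long an event lasts, whether a short pause becomes a long one, and whether a desaturation passes its 5-second minimum.
- **In processing.** Pauses are taken from chest wall movement, a signal exposed to movement artefact. If anyone edits the trace or rejects artefact while seeing the ON/OFF label, the decision can follow the label.

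The result is meant to inform whether a larger trial follows, so a bias of this kind would carry into that decision. Who knows the condition at the bedside is a matter of conduct that has to be settled before the first infant is recorded. A later analysis document cannot restore it.

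**Working it through.** **1. The plan's own figure.** 24 h / 6 h = 4 alternating blocks, of which 2 are ON and 2 are OFF. 2 × 6 h = 12 h per condition. This agrees with the stated 12 hours with and 12 hours without stimulation.

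**2. What randomising the order removes, and what it does not.** Let p1 to p4 be the time effects of the four blocks, T the true effect of one ON block, and B the shift in recorded events per ON block that arises only because someone knows the device is on. The ON-minus-OFF total in one infant has expectation:

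- starting ON: 2T + 2B + (p1 + p3 − p2 − p4)
- starting OFF: 2T + 2B − (p1 + p3 − p2 − p4)

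Averaged over a fair coin flip, the time term cancels and 2T + 2B remains. B has the same sign in both sequences, so the coin flip does not touch it and the paired t-test cannot separate it from T.

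**3. Where B could enter.**

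| Step | What the protocol fixes | What it leaves unsaid |
|---|---|---|
| Order | Coin flip | Who flips the coin, who learns the result |
| Set-up | Pattern set off the unit, Bluetooth then off, no tablet at the bedside | Whether the full 24-hour schedule is stored and switches by itself |
| Disks | Placed on one hand and one foot, sequence run over 24 hours | That they go on before the first block and stay on in both sequences |
| Bedside care | Nothing on this point | Whether staff are told the sequence |
| Event detection | Numeric thresholds, two software packages | Whether anyone edits traces or rejects artefact, and whether labels are visible |

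**4. Sensitivity of the planned test (not an estimate of bias).** The protocol gives no alpha, standard deviation or effect size. Assume n = 25, two-sided alpha 0.05 and a true effect of zero. Let the mean paired difference be shifted by b standard deviations of those differences. The noncentrality is b × √25 = 5b, on 24 degrees of freedom, and the rejection probability is P(|t| > critical value) under that noncentral t distribution.

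| b (assumed) | 5b | Probability of a significant result |
|---|---|---|
| 0 | 0 | 5% |
| 0.1 | 0.5 | 8% |
| 0.2 | 1.0 | 16% |
| 0.3 | 1.5 | 30% |
| 0.4 | 2.0 | 48% |
| 0.5 | 2.5 | 67% |

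The table shows only how the test reacts to a consistent shift. Nothing in the protocol says which row, if any, applies.

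**The case against.** The strongest reply is that silence is not a declaration, and much of it stands.

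- **A reader might infer that the conditions are open to everyone.** The protocol does not say so. Openness is an inference. It is plausible at the bedside, since a motor of the kind described could be felt or heard, and weaker for those who process the files.
- **A reader might infer that the study team scores the recordings by eye.** No scorer is named, and the text ties the study team only to obtaining consent. Events have numeric limits and are evaluated in software. Scoring bias needs a manual step that the protocol neither describes nor excludes. Rules for artefact and label handling might also sit in an analysis plan that is not shown.
- **A reader might infer that infants starting OFF wear the disks for less time.** The natural reading is the opposite: the devices are placed and then run a sequence that may begin OFF. Continuous wear is likely, though not stated outright.
- **A reader might infer that the bias favours vibration.** Staff could respond faster or slower in either condition, so the text supports no direction.
- **Staff can hardly interrupt a pause of 3 to 5 seconds.** This stands for the count of short pauses, and the hypothesis concerns the number of pauses. It does not cover longer pauses, desaturations, bradycardias or durations, all of which are also to be evaluated.

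The reply does not meet the main point. The conduct text is complete from consent to event evaluation and includes no masking measure, and the bedside part cannot be repaired in an analysis plan.

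**Conclusion.** The point holds in a limited form. The protocol compares a perceptible stimulus with its absence and provides no masking of bedside staff or of those processing the recordings, although its own set-up would make some masking feasible. A bias tied to ON versus OFF would recur in every infant, survive randomisation of the order and be read as effect by the paired t-test.

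Its size and direction cannot be derived from the documents; the false-positive rates above depend on assumed shifts, an assumed alpha and 25 infants. The bedside route rests on the inference that staff could notice the vibration. The processing route rests on the possibility of manual editing or artefact rejection. Neither is shown to occur. This is an inexpensive improvement to a pilot; it is not evidence that the comparison is already biased.

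**What to change.** Add three statements to the Study Design procedures:

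1. The disks are applied before the first block and stay in place for all 24 hours in both sequences.
2. The ON/OFF sequence is pre-loaded at the off-unit set-up, if the device can hold it, and is not disclosed to bedside staff.
3. Recordings are exported as coded 6-hour segments without ON/OFF labels. Artefact rejection and event detection are completed before the codes are released.

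The cost is a small file-coding burden with existing equipment and staff. The protocol does not say whether the unit can store a 24-hour schedule, so the pre-loading in the second statement is conditional. The third does not depend on it. Bedside masking will be only partial, since anyone handling the infant may feel the vibration, and the protocol should say so. Processing can be masked to the labels in any case.

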### **Analyses**

This study is a pilot study to determine effectiveness of vibratory stimulation in reducing the number and severity of breathing pauses, oxygen desaturations, and bradycardic events. A relatively small sample size ( $\leq 25$  subjects) will be used to determine effectiveness before a larger randomized-controlled trial will be conducted. The sample size may be adjusted if preliminary results are significantly different than expected (e.g. greater power). We will use within-subjects paired t-tests to assess whether significant changes occur in breathing pauses, oxygen desaturation, and/or bradycardia between periods with and without proprioceptive stimulation.

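### The ON/OFF order is randomised by an unrestricted coin flip and then ignored in a plain paired t-test; balancing the order and adjusting for it is a cheap gain in precision

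*Protocol*

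**What the plan says.** The procedures paragraph of the Protocol (Study Design, under the heading Exclusion Criteria) states that, after consent, "the infant will be randomized by coin flip to start with or without vibration". Vibration is then delivered "in a 6 hour ON/OFF or OFF/ON sequence, for a total of 24 hours". Events are to be counted "with proprioceptive stimulation (total of 12 hours) and without stimulation (total 12 hours), in each study subject".

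The Analyses section names one method: "We will use within-subjects paired t-tests to assess whether significant changes occur" in breathing pauses, desaturation and bradycardia. It mentions no sequence or period term. The Protocol describes nothing that would balance the two starting orders.

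At most 25 infants are planned, with no stated power, effect size or SD, and the number is not firm: "The sample size may be adjusted if preliminary results are significantly different than expected (e.g. greater power").

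**The concern.** The design is a two-sequence crossover with four periods. One group runs ON-OFF-ON-OFF and the other OFF-ON-OFF-ON. A change over the 24 hours that is common to infants, such as a steady drift or settling after the devices are attached, enters the ON−OFF difference with one sign in the first group and the opposite sign in the second. The paired t-test pools the two groups without separating this term.

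Two things follow. The term widens the spread of the differences and so costs power. And since a coin flip does not force equal groups, part of the term remains in the estimate whenever the realised split is uneven. The study is meant to inform a larger randomised trial, so the precision of this estimate matters.

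**Working it through.** **Inputs from the Protocol.** Coin-flip allocation, 6-hour alternation over 24 hours, a paired t-test, and n of at most 25. Reading the schedule as four alternating 6-hour blocks reproduces the stated exposure: 2 × 6 = 12 hours ON and 2 × 6 = 12 hours OFF. The sample size cannot be reproduced because no power calculation is given.

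**Assumptions not in the documents.** The SD of the within-infant difference is set to 1. The period term π is 0, 0.25, 0.5 or 1.0 SD. The vibration effect is τ = 0.584 SD, which gives a paired t-test 80% power at n = 25, two-sided 5%. Power and type I error come from simulation (100,000 runs).

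**Model.** With block effects p1 to p4, infant i has D_i = τ + s_i·π + e_i, where s_i = +1 if ON comes first and −1 if OFF comes first, and π = [(p1+p3) − (p2+p4)]/2.

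- Linear drift of b per block (p = 0, b, 2b, 3b): π = (2b − 4b)/2 = −b. It does not cancel.
- Settling effect c in block 1 only: π = c/2. It does not cancel.
- 24-hour sinusoid or 12-hour day/night pattern: blocks 1 and 3 lie 12 hours apart, as do blocks 2 and 4, so p1+p3 = p2+p4 and π = 0. It cancels.

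**Plain paired t-test.** The mean estimates τ + π(n1−n2)/n. Over coin flips the second part averages to zero, and the standard error is about √[(1+π²)/n]. At π = 0.5 this is √(1.25/25) = 0.224 (simulated 0.223), against a simulated 0.204 with sequence adjustment.

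**Averaged over coin flips, n = 25:**

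| π (SD) | 0 | 0.25 | 0.5 | 1.0 |
|---|---|---|---|---|
| Type I error, paired t | 5.0% | 5.0% | 4.9% | 5.0% |
| Power, paired t | 80% | 78% | 71% | 50% |
| Power, sequence-adjusted | 78% | 78% | 78% | 78% |

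With coin flips kept, the two tests break even between π = 0.2 SD (78.7% against 78.3%) and π = 0.25 SD (77.6% against 78.3%).

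**Conditional on the split.** The exact binomial chance of 16:9 or worse is 23%, of 17:8 or worse 10.8%, and of 18:7 or worse 4.3%. The share of π left in the estimate is 7/25 = 28% at 16:9 and 9/25 = 36% at 17:8.

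- At exactly 17:8 with π = 0.25, 0.5 and 1.0 SD, the shift is 0.09, 0.18 and 0.36 SD, and the type I error is 6.4%, 10.0% and 16.8%. The sequence-adjusted test stays at 5.0%.
- At π = 0.5 SD the paired-t type I error is 3.0% at 13:12, 4.9% at 15:10, 6.9% at 16:9 and 13.9% at 18:7. The 5% average is a mixture of values below and above it.
- Stopping early makes imbalance more likely: the expected |n1−n2|/n is 0.16 at n = 25 and 0.25 at n = 10.

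**Balance alone is not enough.** At 13:12 with π = 0.5 SD, the plain paired t-test has power of 76% or 69%, depending on the direction of the trend. The adjusted test has 80%.

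**The case against.** The best defence is that randomising the order already protects the comparison. A reader might infer from the 17:8 figures that the planned test is biased or has an inflated error rate. It does not: over coin flips it is unbiased and holds 5%, and the higher error rates apply only to splits that are unlikely. This stands. What remains is lost precision, plus a shift that is conditional on the one split obtained.

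The size of the loss is also assumed. For a linear drift, π = 0.5 SD means a change of 3 × 0.5 = 1.5 SD from first to last block, and π = 1.0 SD means 3 SD. The only time trend the Protocol describes (Background and Significance) runs over weeks. This stands too, and it is why a range is shown.

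A reader might infer that day/night rhythm or staff shifts confound the comparison. A simple 24-hour rhythm or 12-hour shift pattern cancels within each infant. No common clock start is stated either, so other clock-linked patterns may differ between infants, and a sequence term would not fully remove them.

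A reader might also infer that allocation is unconcealed or that a flip could be repeated unnoticed. The Protocol is silent on those logistics, it places the flip after consent, and every infant receives both conditions. Silence does not support the charge.

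Finally, this is a pilot, and an SAP that is not shown could add a sequence term. But the Protocol itself names both the coin flip and the paired t-test, so the point concerns what it fixes.

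**Conclusion.** The point holds as a cheap improvement, not as a flaw that invalidates the trial. The planned test is valid on average. It discards the order it has randomised, so a common period effect that survives the alternating blocks becomes noise, and the realised imbalance leaves a share (n1−n2)/n of it in the estimate.

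At n = 25 the power difference runs from negligible at a period term of 0.25 SD, through about 7 points at 0.5 SD (71% against 78%), to about 28 points at 1.0 SD (50% against 78%). Below about 0.2 SD, with coin flips kept, adjustment gains nothing. These figures rest on the assumed period term, the assumed effect of 0.584 SD and the four-block reading of the schedule. The mechanism, the binomial chances and the residual share do not depend on the size of the period term.

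**What to change.** 1. Assign the starting condition from a pre-generated permuted-block list with varying block sizes, each assignment revealed only after consent.
2. In Analyses, replace the plain paired t-test by a regression of each infant's ON−OFF difference on sequence coded +1/−1, and test the intercept on n−2 degrees of freedom. The intercept is the average of the two sequence means, so it is free of the common period term at any split.

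Both parts are needed: the list keeps the groups near equal, and the sequence term recovers the power.

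Do not substitute a four-block mixed model whose only random term is an infant intercept. It is not equivalent: it ignores variation between infants in the response to vibration and tests on about 71 residual degrees of freedom (100 blocks − 25 infants − 3 periods − 1 condition) instead of 23. If that variation has an SD of 0.5 or 1.0 times the block-level residual SD, its type I error is about 7.5% or 11%.

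**Cost.** A short list, one changed sentence and one degree of freedom. With no period effect, power falls from about 80% to 78% if coin flips are kept, and hardly at all under blocking (80.2% against 79.9% at 13:12). Carry-over between blocks is a separate matter that this change does not address.
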